#### Birth Weight and Gestational Age

Trained field research assistants measured the birth weight of the neonate within 72 hours of birth. In the intervention clusters, the peer counselors provided delivery information to the research team in timely fashion. In the case of control clusters, we recruited volunteers responsible for the timely reporting of the delivery information.

#### Child Morbidity

The interviewers obtained illness histories, such as diarrhea, dysentery (blood and mucus), fever and cough, and ear infection (purulent discharge), every month until 12 months, and at 3-month intervals until 18 months using the 2-weeks' recall method. The questions asked were based on the standard DHS infant morbidity recall questions but were expanded to include questions about ear discharge.

Diarrhea was defined as an episode of the passage of 3 or more loose or watery stools within 24 hours. The presence of blood in the stool was defined as invasive diarrhea. When a single episode of diarrhea lasted for more than 2 weeks, it was be classified as persistent diarrhea. Acute respiratory illnesses were defined as an episode of cough with reported fast and rapid breathing or difficulty breathing with or without fever.

#### Child Development

We collected a variety of child development measures at 9, 18, 24, 36, and 48 months. The Ages and Stages Questionnaire [38] was used to collect data on problem-solving, socioemotional, communication, and fine and gross motor functions at 9 and 18 months of age. The Bayley Scales of Infant and Toddler development-III (Bayley-III) [39] was used to assess children's cognitive, language, and motor development at 24 and 36 months of age. The test is not standardized in Bangladesh but has been culturally adapted and used in several studies on Bangladeshi children [40,41]. The Wechsler Preschool and Primary Scale of Intelligence (WPPSI) [42] will be used on a subsample of children at 48 months to assess their full scale, verbal, and performance IQs. The children's behavior during the Bayley test was rated using 5 behavior ratings developed by Wolke et al [43], each of which has ratings from 1 to 9, with 1 being the poorest behavior and 9 being the best. We interviewed mothers on child behaviors using the Strengths and Difficulties Questionnaire [44] at 48 months after the WPPSI test.

The Movement Assessment Battery for Children [45] will be administered along with WPPSI at 48 months of age on the same subsample.

Information on quality of home stimulation was assessed by a family care indicators questionnaire [46] at 9, 18, and 24 months. An early childhood version of the home observation for measurement of the environment [47] was administered at 24 and 36 months to collect information on approaches that the family employs, such as availability of toys, books, musical instruments, play activities with the child, and other learning opportunities at home.

#### Maternal Depression

We assumed that the mother's mental well-being or depression condition could affect the child's nutrition and caring practices, which can mediate child development. We collected information regarding the mothers' mental status and depression conditions in the third trimester of pregnancy and at 1 and 10 months postpartum from all participants using the Center for Epidemiological Studies-Depression questionnaire [48].

Maternal IQ was measured using the Raven Coloured Progressive Matrices [49].

#### Socioeconomic Status

Information on religion, pregnant women's and her husband's levels of education, their occupations, number of family members, ownership of the number of dwelling rooms, household construction materials, toilet facilities, drinking water sources, household assets, and land ownership were collected as the key indicators of socioeconomic status.

#### Household Food Security

As household food security plays a vital role in complementary feeding practices and child nutrition, we assessed the family's food security from all participants (during enrolment and at 10 months).

#### Information on Social Network

Family members, friends, neighbors, peers, and people around caregivers play important roles in feeding and caring for young infants. Therefore, we collected information on the social networks of caregivers at different times of follow-up from 100 families in 4 clusters.

### Schedule of Data Collection

We carried out a pilot study in the first year of the trial in a single cluster to test the recruitment methods, implementation of the intervention, the evaluation of instruments, and field methods before commencing the trial.

For the assessment of trial outcomes, we collected basic sociodemographic information about the family and maternal characteristics in a baseline survey at enrolment. We recorded the details of the birth and pregnancy shortly after delivery. We assessed the trial outcomes by measurements at monthly intervals from birth until 12 months, at 3-month intervals until 18 months, and annually until 48 months. These included anthropometric measurements, the recording of dietary patterns, dietary intake, and morbidity. The schedule of data collection is given in Figure 3.

### Process Evaluation

We conducted a mixed methods process evaluation within the Mirpur Shishu Pushti Trial to answer the primary question of how and why or why no impacts were achieved [50,51]. The specific aims included the assessment of fidelity, dose, reach, and intensity of the peer counseling intervention; the response of the beneficiaries to the intervention; experience of the peer counselors of counseling the women; and the barriers and challenges encountered by the project staff to implement the trial.

We further aimed to synchronize the process evaluation data collection with the timeline of program implementation. Data collection has been planned to occur in 2 stages: (1) ongoing throughout the intervention delivery and (2) at a time point near the end of the intervention. This approach will enable us to use the process evaluation data for both providing feedback to keep the program on track (formative use) and to interpret and explain intervention outcomes (summative use) [52].

We collected the data for the process evaluation through regular project monitoring on the participation of mothers in peer counseling sessions, surveys of self-reported adherence to counseling guidelines by the peer counselors, unscheduled direct observations of the peer counseling at-home visits, in-depth interviews of mothers, semistructured interviews with the project managers (GA) and the project field staff, and focus group discussion with peer counselors. We collected the data in a purposively selected sample of intervention clusters to cover the variations within the households.

### Sampling Design and Sample Size

The sample size required was 1950 mother-infant dyads (975 in each treatment group) from 50 clusters with 39 mother-infant dyads per community cluster recruited over 3 months. The sample size calculation was estimated with the following assumptions: Each community cluster had an average population of 70,000 and an expected crude birth rate of 4.3 per 1000 total population over 6 months (based on the crude birth rate for urban Bangladesh of 25.8/1000 population over 36 months from the 2004 Bangladesh DHS]) thus giving an average expected number of births of 150 over 3 months per cluster. Previous research [34] indicated that appropriately 33% of pregnant women returned to their home village following delivery, leaving an expected number of eligible births of 200 over 6 months per cluster. We anticipated having 39 mother-infant dyads per cluster, assuming 95% participation but 22% loss to follow-up based on earlier research [34] from the approximately 200 mother-infant dyads available in each cluster over 6 months. We also assumed 90% power and a 5% two-sided α and intracluster correlation coefficient of 0.015 (based on analyses of the child anthropometric measurements from the 2004 Bangladesh DHS survey data for urban child populations [53]). We also expect the difference in the prevalence of stunting between the treatment groups of 10% (35% in control to 25% in the intervention group), which is similar to the change reported in an earlier education intervention for young child feeding in Peru [54]. 

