### Identification of Clusters

The study site is a very densely populated and includes areas of slum housing where there are no established addresses and houses are very close to each other against each other along narrow paths. In this setting, there were no administrative or natural boundaries to define clusters. For the trial, we used satellite maps of the study areas in Mirpur to define clusters with buffer areas. We digitalized all structures, buildings, roads, and water bodies from satellite maps of the study area and gave each structure an identification number. Our field census team visited all the structures and buildings in the study area and identified if it was a residence or was used for other purposes. After obtaining written informed consent, we conducted a brief household census and screened for pregnant women in all residential buildings. We used the census data to create a population database linked to the mapped structures. Using geographic information system mapping techniques, we constructed 36 clusters from the population maps to cover an average population of 5000 people with a surrounding 200-meter buffer zone between clusters. We classified each cluster as low socioeconomic status or not based on the census data. Figure 2 shows a map of the study site.

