### Assignment of Treatments

We randomly allocated the 36 clusters in an equal ratio to intervention or control groups but with stratification by socioeconomic status of the clusters. We generated the random allocation sequence using SAS software (SAS Institute).

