## Results

Using satellite maps, we digitized all structures in the study areas, and from a brief census of all mapped residences, we identified a population of 65,535 people. We created a population database linked to the map structure and applied this information to define 36 clusters with 500-meter buffer zones. We randomly allocated the 36 clusters in an equal ratio to intervention or control groups but stratified by the socioeconomic status of the clusters. We screened for pregnant women in all residences and identified 5377 eligible pregnant women.

From July 2011 to May 2013, we carried out a baseline survey. In the third trimester, we examined 2050 pregnant women, including 1056 women in the intervention group and 994 women in the control group. The women participating in the trial had 1883 birth outcomes, with 993 in the intervention group and 890 in the control group. The study followed up the women who delivered the infants until 18 months of life. In December 2012, we began assessing the original cohort and completed 18 months of study follow-up in October 2014 for participants. Among them, 692 in the intervention group and 551 in the control group remained in the study until 18 months follow-up, with 301dropouts in the intervention and 339 dropouts in the control group. We continued evaluating the cohort until the children were 36 months of age, with child growth and development outcomes measured at 24 and 36 months. The long-term follow-up began in January 2015 and ended in February 2017. We have now completed the data cleaning and processing and have started analyses of the data.

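### Sample size and 90% power are stated for 50 clusters of 70,000 people, but 36 clusters were randomised and no power is given for them

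*Protocol article*

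**What the plan says.** In the protocol article, Sampling Design and Sample Size gives the requirement: "The sample size required was 1950 mother-infant dyads (975 in each treatment group) from 50 clusters with 39 mother-infant dyads per community cluster". It describes the clusters as follows: "Each community cluster had an average population of 70,000". The statistical inputs are "We also assumed 90% power and a 5% two-sided α and intracluster correlation coefficient of 0.015" and a stunting difference of "10% (35% in control to 25% in the intervention group"). It derives 39 dyads per cluster from roughly 200 available over 6 months, allowing for 95% participation and 22% loss to follow-up. The opening sentence of the same section puts recruitment over 3 months.

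Other sections describe a different design:

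- Assignment of Treatments: "We randomly allocated the 36 clusters in an equal ratio to intervention or control groups".
- Identification of Clusters: "we constructed 36 clusters from the population maps to cover an average population of 5000 people with a surrounding 200-meter buffer zone between clusters".
- Results, on the census: "from a brief census of all mapped residences, we identified a population of 65,535 people".
- Results, on the clusters: "applied this information to define 36 clusters with 500-meter buffer zones".

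Selection and Training of Peer Counselors fits 36 clusters, with 18 counselors trained, one per cluster. Results reports 2050 women examined in the third trimester, 1883 birth outcomes, and 692 intervention and 551 control children remaining at 18 months.

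**The concern.** In a cluster trial, the number of clusters is part of the power statement. A reader who takes the section at face value will credit this trial with 50 clusters and 90% power on that basis. The randomised trial has 14 fewer clusters, and the article gives no figure for it. The primary comparison is stunting at 18 months, and a null result would be read against the stated power.

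The inputs also cannot all be true together. One planned cluster of 70,000 is larger than the whole census reported in Results. The buffer, which is the stated geographic separation between clusters, has two widths. The per-cluster yield does not follow from the percentages given for it.

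**Working it through.** **Inputs** (Sampling Design and Sample Size unless noted): 35% vs 25%; two-sided 5%; 90% power; intracluster correlation 0.015; 39 dyads per cluster; 95% participation; 22% loss. Clusters randomised: 36 (Assignment of Treatments). Children at 18 months: 692 and 551 (Results).

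**1. Reproducing 1950.**
- Uncorrected n per arm = [1.96 x sqrt(2 x 0.30 x 0.70) + 1.2816 x sqrt(0.35 x 0.65 + 0.25 x 0.75)]^2 / 0.10^2 = 439.2, rounded up to 440.
- With continuity correction: (439.2 / 4) x [1 + sqrt(1 + 4 / (439.2 x 0.10))]^2 = 459.01, rounded up to 460.
- Design effect = 1 + (39 - 1) x 0.015 = 1.57.
- 460 x 1.57 = 722.2; / 0.78 = 925.9; / 0.95 = 974.6, so 975 per arm and 1950 in total.
- 975 / 39 = 25 clusters per arm, 50 in total.

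The stated 1950, 975 and 50 all come out. Without the continuity correction, 440 x 1.57 / 0.78 / 0.95 = 932.3, so 933 per arm and 1866 in total, which does not match.

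**2. What that route requires.** The article does not mention a continuity correction. The route also uses 39 in two roles: as the cluster size in the design effect, which should be children analysed, and as the divisor of 975, a number before participation and loss. The two readings differ:
- 39 before losses: 39 x 0.95 x 0.78 = 28.9 analysed per cluster, 722 per arm, design effect 1.418. Power in 50 clusters is 93.7% (92.8% continuity-corrected).
- 39 analysed: 975 analysed per arm, design effect 1.57. Power is 97.1% (96.7% continuity-corrected).

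Both exceed 90%, so the ambiguity errs on the conservative side.

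**3. Yield per cluster.** 70 x 4.3 = 301 births over 6 months, about 150 over 3 months. After 33% leave, 301 x 0.67 = 202, the stated 200 or so. The next step fails: 200 x 0.95 x 0.78 = 148, not 39. Over a 3-month window it is 100 x 0.95 x 0.78 = 74, still not 39.

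**4. Power of the randomised design**, 18 clusters per arm, correlation 0.015, equal cluster sizes within each arm.
- *1950 recruited, read as the number before both allowances:* 975 x 0.95 x 0.78 = 722 analysed per arm, 40.1 per cluster. Design effect = 1 + 39.1 x 0.015 = 1.587; effective n = 455. Power = Phi[(0.10 x sqrt(455) - 1.96 x sqrt(0.42)) / sqrt(0.415)] = 91.0%, or 89.8% continuity-corrected.
- *Retained at 18 months:* 551 / 18 = 30.6 and 692 / 18 = 38.4 per cluster; design effects 1.444 and 1.562. SE = sqrt(0.2275 x 1.444 / 551 + 0.1875 x 1.562 / 692) = 0.0319. 0.10 / 0.0319 = 3.13. Power is Phi(3.13 - 1.96) = 88%, or 86% by noncentral t on 36 - 2 = 34 df.

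**5. Populations and buffer.**

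| Quantity | Figure | Section |
|---|---|---|
| Cluster population | 70,000 | Sampling Design and Sample Size |
| Cluster population | 5000 (x 36 = 180,000) | Identification of Clusters |
| Census total | 65,535 (/ 36 = 1820) | Results |
| Buffer | 200 m | Identification of Clusters |
| Buffer | 500 m | Results |

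The planned 50 x 70,000 = 3.5 million people is far beyond the census in Results.

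**The case against.** The strongest reply is that the calculation is sound. It returns 1950, 975 per arm and 50 clusters together, using percentages that all stand in the section plus a standard correction. On this view the section preserves the original plan, which is plausible because the article says it merges two approved protocols, and moving to 36 clusters costs almost nothing at the planned total.

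Much of that stands, and it rules out several stronger readings:

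- **That 1950 is an arithmetic error.** A reader who stops at 440 x 1.57 = 691 per arm might infer this, but that figure is before losses and 975 is after allowing for them.
- **That 36 x 39 = 1404 analysed dyads is the true requirement, which the trial missed.** The documents set no such target. It rests on an uncorrected formula and on 39 being the number analysed. The lower number of children at 18 months reflects attrition, not an error in the plan.
- **That 50 is a slip for 50 dyads per cluster.** Step 1 shows that 50 clusters follows from the calculation.

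The reply does not cover the absence of any statement that the 50-cluster design was superseded, or of any power for the design that was. A condensed article may leave detail to the full protocol. These are not omitted details, however: they are printed figures that contradict one another. The double use of 39, the 148, the populations and the buffer widths also remain.

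**Conclusion.** The point holds as an unreconciled design description. The cluster number and power basis stated for the trial are not those of the trial that was randomised, and the supporting figures for yield, cluster population, census and buffer conflict within the article. It does not hold as a claim that 1950 is wrong or that the trial is badly underpowered.

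The size is modest. Under the article's own rates and correlation, 36 clusters give about 90-91% with 1950 recruited, and 88% (normal) or 86% (t, 34 df) with 1243 children retained. Most of the drop below 90% comes from attrition: 301 / 993 = 30% and 339 / 890 = 38% after birth, against 22% planned. These powers assume equal cluster sizes within arm and a correlation of 0.015. Unequal clusters or a higher correlation would lower them. The article gives no values for cluster-size variation.

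**What to change.** 1. Keep the existing calculation, labelled as the original plan. Give its formula, including the continuity correction if one was used, and say whether 39 per cluster is recruited or analysed.
2. State that 36 clusters (18 per arm) were randomised, and when and why this replaced 50.
3. Give power for 36 clusters at a correlation of 0.015: about 90-91% (normal) for 1950 recruited and about 722 analysed per arm, and about 88% (normal) or 86% (t, 34 df) for 692 + 551 children at 18 months. Mark the latter as calculated after follow-up.
4. Correct the chain from births to dyads per cluster, using one recruitment window.
5. Reconcile cluster population, census total and buffer width from the mapping and census files, and use one value of each throughout.

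The cost is rewording, a short recalculation and a look-up in existing files, with no new data. The downside is that the stated power becomes slightly less favourable.

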### Statistical Analyses

Data analysis will be by intention to treat. Analyses will be conducted at the mother-infant dyad level but will be adjusted for the community-cluster randomization [55]. The primary analyses will compare the prevalence of stunting (length-for-age < –2 *z* score) in children at 18 months of age using Pearson chi-square tests and 95% CIs for the group difference, with adjustments for clustering. We will report the results for 2-sided 5% tests.

Secondary analyses will examine each outcome variable (length-for-age, percentage EBF, duration of breastfeeding, percentage doing bottle feeding, percentage giving complementary feeds, percentage receiving diverse food groups, and mean nutrient intakes), taking account of the repeated measurements within children by using separate mixed models. We will use linear mixed models for the continuous outcomes (eg, height for age *z* score, duration of breastfeeding, Ages and Stages Questionnaire, Bayley, and Wechsler scales) and generalized linear mixed models for noncontinuous outcomes (eg, logistic mixed models for binary outcomes, such as percentage stunted or percentage exclusively breastfeeding). Models will include the treatment group as a fixed effect and infants as a random effect to account for the repeated measurements, and community cluster as a random effect to account for the cluster effect. The models will evaluate the impact of the interventions over time by testing for an interaction between time and the intervention group.

We will conduct analyses to identify the baseline characteristics of the mother-infant dyads who may benefit most from the intervention. Model assumptions will be checked, and appropriate adjustments to the analysis will be made where necessary. We will use Stata software (Stata Corp) for all analyses, with the “mixed” command to fit linear mixed models, the “melogit” command to fit mixed-effects models for binary outcomes, and the “mepoisson” command to fit mixed-effects models for event count data.

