### Recruitment, Inclusion and Exclusion Criteria, and Consent of Mothers and Their Families

We visited the pregnant women identified in the census, and recruited eligible women in their third trimester of pregnancy into the trial. We updated the census data, including the pregnancy screening, every 3 months to identify and recruit potentially eligible women once they reached their third trimester. We included pregnant women who were 16 to 40 years of age and who had no more than 3 living children. We excluded women who planned to migrate from the Mirpur area after delivery and women with medical records of heart disease, tuberculosis, gestational diabetes, or eclampsia in previous pregnancies, from the trial. In addition, we excluded mother-infant pairs where the child had congenital abnormalities, had a very low birth weight below 1.5 kg, or were admitted to a neonatal intensive care unit. We used the same approach to recruitment in both intervention and control clusters. Trained project staff obtained written informed consent from the eligible women and their husbands. Based on experience with similar projects in Bangladesh [33,34], we expected at least 95% of the mothers would consent to participate. We anticipated excluding up to 30% of the women mainly related to their desire to migrate back to their home village after the delivery [34].

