### Measurements

#### Anthropometry

Trained research assistants collected the anthropometric measurements (weight and height) using established methods [36] and recorded these measurements on both the research instruments and an infant growth chart for the mother to keep. We standardized these measurements before and during the data collection. Anthropometry was collected soon after birth and every month up to 12 months, at 3-month intervals up to 18 months (15 and 18 months), and then at 24, 36, and 48 months. We used the 2006 WHO growth standards to construct anthropometric indices. We calculated the standard WHO-recommended indicators to assess stunting (height-for-age <–2 *z* score), wasting (weight-for-height <–2 *z* score), and being underweight (weight-for-age <–2 *z* score).

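### The primary 18-month chi-square uses only children measured at that visit, although dropout is 30.3% vs 38.1% by arm and earlier lengths that could reduce the resulting bias are in hand

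*Protocol article*

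**What the plan says.** The Statistical Analyses section of the protocol article opens with the principle "Data analysis will be by intention to treat". It then sets the primary comparison as stunting prevalence "in children at 18 months of age using Pearson chi-square tests and 95% CIs for the group difference, with adjustments for clustering". Models "taking account of the repeated measurements within children by using separate mixed models" appear in the next paragraph as secondary analyses. They include a logistic mixed model for stunting with infant and cluster random effects and a time-by-group interaction.

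The Anthropometry section describes a dense series of lengths: "Anthropometry was collected soon after birth and every month up to 12 months, at 3-month intervals up to 18 months".

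The sample size was set "assuming 95% participation but 22% loss to follow-up based on earlier research". The Results section reports "2050 pregnant women, including 1056 women in the intervention group and 994 women in the control group", then 993 and 890 birth outcomes, then 692 and 551 children remaining at 18 months, "with 301dropouts in the intervention and 339 dropouts in the control group". No reasons for dropout are given.

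The recruitment section also removes some infants after birth: "we excluded mother-infant pairs where the child had congenital abnormalities, had a very low birth weight below 1.5 kg", together with those admitted to neonatal intensive care.

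**The concern.** A chi-square on stunting at one visit can count only children with a length at that visit. Adjusting it for clustering corrects the standard error but does nothing about children who are absent. As the plan stands, the primary result compares the retained children of each arm. The arms have kept different shares of their births, and overall loss is well above the planned figure.

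There are reasons in the document to think retention could depend on arm. Peer counselors reported deliveries in intervention clusters, while recruited volunteers did so in control clusters, and only intervention families had the scheduled counseling visits. The document also expects families to return to home villages and expects working women to be hard to retain. Such factors could be related to child growth, although the document does not show that they are.

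At stake is whether the primary difference reflects the effect of counseling or partly reflects who stayed. A child seen at 15 months but not at 18 contributes nothing to the primary test, although up to 14 earlier lengths may be on file (one after birth, twelve monthly, one at 15 months).

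**Working it through.** **Planned figure.** For 35% vs 25% with 90% power and two-sided 5%, a two-proportion calculation with continuity correction gives 460 per arm. The design effect is 1 + (39 − 1) × 0.015 = 1.57, and 460 × 1.57 = 722.2. Dividing by 0.78 (22% loss) and by 0.95 (participation) gives 974.6, which matches the stated 975 per group. So 22% is the loss that the plan allowed for.

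**Observed loss (Results section).** The counts reconcile: 993 − 692 = 301 and 890 − 551 = 339.
- Intervention: 301/993 = 30.3%
- Control: 339/890 = 38.1%
- Overall: 640/1883 = 34.0%, leaving 692 + 551 = 1243 children
- Gap: 7.8 points
- From enrolment, no 18-month data: 364/1056 = 34.5% vs 443/994 = 44.6%. No recorded birth outcome: 63/1056 = 6.0% vs 104/994 = 10.5%.

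**Could the gap be chance?** The pooled standard error is √[0.340 × 0.660 × (1/993 + 1/890)] = 0.0219. Then z = 0.0778/0.0219 = 3.56, and p = 0.0004 ignoring clustering. The document gives no intracluster correlation (ICC) for dropout. Its 0.015 is for anthropometry, so a range is assumed. The mean cluster size is 1883/36 = 52.3:
- ICC 0.015: design effect 1.77, p = 0.007
- ICC 0.03: design effect 2.54, p = 0.026
- ICC 0.05: design effect 3.57, p = 0.060

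**Possible bias.** Within an arm, prevalence among all births = prevalence in retained children + loss × d, where d is prevalence in lost minus retained children. With benefit defined as control minus intervention:

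bias in the retained-children benefit = 0.303 × d(intervention) − 0.381 × d(control)

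Every value of d below is an assumption.
- d = 10 points in both arms: 3.0 − 3.8 = −0.8 points (benefit understated)
- d = 10 points in control only: −3.8 points (benefit understated)
- d = 10 points in intervention only: +3.0 points (benefit overstated)

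For selection in opposite directions, suppose there is no true effect (35% in both arms) and lost children are stunted in 40% (intervention) and 30% (control). Retained prevalence is then (0.35 − 0.303 × 0.40)/0.697 = 32.8% and (0.35 − 0.381 × 0.30)/0.619 = 38.1%, a spurious benefit of 5.3 points. Exchanging the two assumed rates gives 5.3 points of apparent harm.

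**Precision.** With 692 and 551 children in 36 clusters and ICC 0.015, power for 35% vs 25% is still about 88%. The issue is mainly bias.

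**The case against.** The strongest reply has five parts.

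**The term is inferred.** The article never calls the analysis completers-only and defines no analysis set. Missing-data handling is often left to an analysis plan, and none is shown. This stands as far as it goes: the absence of an imputation section is not the point. The point is the method the article names as primary, set against the attrition it already reports.

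**A remedy is already planned.** The logistic mixed model for stunting uses all visits. True, but only as a secondary analysis, and not presented as a check on the primary result.

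**The bias may be small or conservative.** A reader might infer that the chi-square is valid only if loss is completely at random within arm. That is too strong. Similar selection in both arms largely cancels, and at the observed rates a common 10-point difference moves the result by only 0.8 points. A reader might also infer that unequal loss favors the intervention. The document does not support that either: if lost children are more stunted in both arms or in control only, the benefit is understated. A spurious benefit needs another assumed pattern.

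**The dropout count is coarse.** The denominators are birth outcomes and no reasons are given. Stillbirths, deaths and post-birth exclusions may be included, so 34.0% need not all be loss to follow-up. The timing of dropout is also unreported. If families left soon after delivery, few of the 14 possible lengths exist for them.

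**A late switch has its own cost.** Data are cleaned, analyses have started, and attrition by arm is known. This stands and shapes the fix.

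**Conclusion.** The point holds in a limited form. The analysis fixed as primary makes no use of the earlier lengths, under loss that is higher than planned and unequal by arm. The estimate is open to bias, but neither its direction nor its size can be learned from the document. The illustrations run from 0.8 points to about 5 points against a planned effect of 10, all on assumed stunting rates in lost children. Evidence that loss truly differs by arm ranges from strong (p = 0.007) to borderline (p = 0.060), depending on the assumed ICC for dropout.

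Two stronger conclusions are not supported: that the result will be biased, and that the intention-to-treat principle has been broken to an extent that matters. The post-birth exclusions do follow allocation and antenatal counseling. However, they are stated as eligibility criteria, recruitment used the same approach in both arms, and no counts are given, so they call for reporting only. This is an inexpensive improvement that should be made, not a fatal flaw.

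**What to change.** Estimate the 18-month stunting difference from all available lengths, by one of two routes:
- Multilevel multiple imputation of 18-month length-for-age, done by arm with a cluster effect. Use lengths from birth to 15 months and baseline covariates, then apply the −2 z cut-off. Restrict imputation to children not known to have died.
- The 18-month contrast from the logistic mixed model already planned, converted to a risk difference.

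Make this the primary estimate, or at minimum a named key analysis beside the chi-square. Add a delta-shift sensitivity analysis in which the shift for unobserved children may differ by arm. Report dropout reasons, timing and post-birth exclusions by arm, and include excluded infants in a sensitivity analysis where they were measured.

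The cost is a few days of analysis and no new data. There are two downsides. The estimate relies on a missing-at-random model, which the delta analysis probes. It is also a change made after analyses have started, so it must be dated and declared, with the planned chi-square still reported in full.
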